#### Inflammatory mechanisms

Another secondary outcome is inflammation, given our data that sleep disturbance impacts circulating markers of inflammation, cellular production of inflammatory cytokines, and activation of inflammatory signaling; that improvements in sleep disturbance are associated with decreases in cellular inflammation; that activation of inflammatory signaling is found in those with a history of depression; and that increases of systemic markers of inflammation are associated with depression. We will assess inflammatory biology dynamics using a vertically integrated mechanistic approach and examine upstream signaling pathways, cellular production of proinflammatory cytokines, and circulating levels. Circulating levels and cellular markers of inflammation are assessed by assay of plasma inflammatory biomarkers (IL-6, CRP) in duplicate by ELISA and stimulated monocyte production of IL-6 and TNF by flow cytometry. We will assay IL-6 and CRP because of our theoretical focus on inflammation and evidence that these two markers of inflammation are associated with depression. In addition, we will focus on a select set of cellular and circulating markers given our preliminary findings, and the association of these markers with sleep disturbance and/or depression risk. Inflammatory signaling will be measured by assay of activation of NF- $\kappa$ B using intranuclear staining and flow cytometric analyses.

#### Biobehavioral and medical factors

Other variables will be examined because these factors can contribute to changes in inflammatory outcomes, including health and daily functioning (i.e., *Medical Outcomes Study Short-form, SF-36*\*79-81); mental health (i.e., Beck Anxiety Inventory) and psychosocial stress (i.e., Perceived Stress Scale); physical activity (i.e., *Godin Leisure-*

*Time Exercise Questionnaire*). At baseline, we will evaluate subject characteristics that have been related with depression risk including sex, race/ethnicity, education, household income, marital status, and severity of medical co-morbidity (i.e., Charlson Co-Morbidity Index). Age range in the present sample is restricted to those older than 60 years.

## **6. Interventions**

### Cognitive behavioral therapy for insomnia (CBT-I)

Cognitive behavior therapy for insomnia (CBT-I) is a multicomponent (i.e., behavioral, cognitive, educational) intervention as previously described by Morin et al. Briefly, as described below, CBT-I contains five validated components: cognitive therapy, stimulus control, sleep restriction, sleep hygiene, and relaxation, which together target sleep-related physiologic and cognitive arousal to reestablish restorative sleep function. The content of the intervention is organized around a series of modules that is presented to patients in manualized form. CBT-I includes five treatment modules: (1) *Cognitive Therapy* uses cognitive restructuring principles to help patients identify maladaptive sleep cognitions, neutralize their effect, and facilitate more adaptive thinking about sleep and its importance, including training in other cognitive coping strategies such as relaxing self-talk, imagery, and distraction methods (e.g., repetition of a calming phrase, thought); (2) *Stimulus Control* targets sleep behavior directly by instructing patients to go to bed only when sleepy; use the bed only for sleep and sexual activity and not other behaviors that compete with sleep; leave the bedroom after being unable to fall asleep within 20 minutes; repeat this process as often as necessary either before falling asleep or after awakening from sleep; and establish and adhere to a fixed time of arising each morning. (3) *Sleep restriction* was used to limit the amount of time spent in bed to the amount of time spent sleeping. This method creates a mild state of sleep deprivation and is thought to lead facilitate a faster sleep onset and greater sleep

continuity and quality. Specifically, the window of time available to sleep is altered weekly to approximate a sleep efficiency goal of 85%. Sleep efficiency was monitored weekly by sleep diary, and when sleep efficiency was less than 80%, the sleep window was decreased by 15 to 20 minutes per night. The sleep window was not decreased to less than 5 hour a night because this level of restriction can lead to daytime drowsiness and related adverse events which were monitored during treatment as described below.

(4) *Sleep hygiene* provides sleep education and discussion of the role of biological, psychological, social, and behavioral factors that affect sleep, such as stress, cognitive arousal, poor sleep hygiene, and mood disturbance; (5) *Relaxation* assists patients in developing behavioral goals in areas where sleep has disrupted their functioning and mood (e.g., work, social, physical activity), with the use of self-rewards (e.g., leisure, resting, relaxation), scheduling of pleasant events and mental exercises to increase relaxation and awareness of positive emotional states. Addressing relaxation and mood throughout the protocol in an integrated manner is believed to augment the efficacy of the intervention in those who have high rates of depression such as older adults with sleep disturbance, and also contribute to the maintenance and generalization of the intervention during follow-up. We will also provide *Skill Consolidation and Adherence* which is devoted to the development of individual treatment plans for follow-up, including performance of skills, and insomnia remission maintenance training methods to help patients cope with situations that have contributed to poor sleep disturbance or that have interfered with the implementation of the treatment. The final week of treatment includes the development of a CBT-I adherence plan to ensure continuity of practice and skill maintenance during follow up.

CBT-I is administered in groups of 5-10 subjects by a licensed clinical psychologist who also had received specialty training in behavioral medicine, including delivery of CBT-I. Treatment with CBT-I in individual- or group based formats has been

found to be equally efficacious. Prior to delivery of CBT-I, this clinical psychologist will be supervised by a non-study therapist (i.e., a therapist who is not a key personnel or part of the investigative team, and who is not involved in delivery of the intervention during the trial) with over two decades of experience in CBT-I treatment of insomnia, who will confirm competency of study therapist and delivery of CBT-I using the study manualized approach. During delivery of the intervention, the non-study therapist randomly attends at least two CBT-I sessions and rates fidelity of CBT-I delivery of the five components described above using a 5-point scale for each component of CBT-I, as well as overall competency.

Clinician-delivered CBT-I was selected for this study because this delivery format yields greater and more durable effects, with higher rates of adherence and retention, than digital CBT-I.

The CBT-I followed delivery of CBT-I using a manualized approach, in which each session dictated objectives, patient skills, and treatment activities. The CBT-I sessions are held once a week for 120 minutes (each session) over the 8-week treatment period, identical to the time schedule which is used for Sleep Education Therapy (SET). For each session, the CBT-I treatment manual outlines objectives, patient skills, and treatment activities. Therapists direct role-playing and other skill-development exercises that are designed to increase patients' self-efficacy in managing their insomnia.

Homework, totaling about one hour of dedicated time outside of sessions, was assigned weekly to ensure practice and skill application.

Adherence at end of treatment will be assessed by reported willingness to adhere to the assigned insomnia treatment.

#### Sleep Education Therapy

Sleep Education Therapy (SET) is group-based manualized course in sleep hygiene and sleep education that matches the CBT-I condition expectancy of beneficial effects.

SET is an active comparator control condition which is known to produce modest benefits in insomnia, although these improvements are not as robust or durable as found with CBT-I. SET uses a manual that presents educational information and describes learning objectives and patient activities to promote integration of material. SET follows a didactic format, inviting experts to lecture on 5 key topics, followed by focused group discussion, and post-discussion self-help quizzes to assess patient learning. Topics include: 1) Basic Facts about Sleep; 2) Sleep Hygiene; 3) General Health and Aging; 4) Complementary Medical Approaches and Health Factors relating to sleep; 5) Relating to the Health Care System. Educational and behavioral change content is based on the National Sleep Foundation's tips for better sleep, including changing poor sleep habits, avoiding stimulants such as coffee and tea near bedtime, exercise and relaxation, adequate exposure to natural light, establishing a relaxing bedtime routine, and modification of sleep environment to be relaxing and not distracting.

SET is also administered in groups of 5-10 subjects by a public health educator with a Master's level degree in public health, who had specialty training in behavioral medicine as a clinical psychologist. Prior to delivery of SET, this person was supervised by a non-study therapist who had experience in the delivery of SET in community settings to improve sleep outcome. The non-study therapist with experience in public education will confirm therapist competency. Similar to fidelity rating for CBT-I, the non-study therapist with experience in public health education randomly attended SET sessions and rated fidelity of SET delivery of the five components described above. We will also provide *Skill Consolidation and Adherence* which is devoted to the development of plans for follow-up, including how to integrate the educational information and sleep hygiene skills into daily life. The final week of treatment includes the review of the education material and plans for development of a SET adherence plan to ensure use of educational material during follow up.

Using a manualized approach, each session dictates objectives, patient skills, and treatment activities. The SET sessions are held once a week for 120 minutes (each session) over the 8-week treatment period, identical to the time schedule which is used for CBT-I.

Practice of the sleep hygiene behaviors and reading on healthy sleep was assigned as homework each week so that SET intervention to matched the homework assigned to CBT-I. This home assignment totaled about one hour of dedicated time outside of SET sessions.

Adherence at end of treatment will be assessed by reported willingness to adhere to the assigned insomnia treatment.

## **7. Randomization and allocation concealment**

### Sequence generation

Randomization sequence will be generated via computerized random number generator in blocks of 5-10 participants in CBT-I and SET(1:1).

### Allocation concealment

Allocation concealment will be maintained using sequentially numbered, opaque, and sealed envelopes.

## **8. Blinding**

Participants will be aware that they would be assigned to a group for the treatment for insomnia. The consent form stated that participants would be assigned at random to either CBT-I and SET, and that both treatments are used to treat insomnia. However, participants were partially blinded; they were aware of receiving a treatment for insomnia, but were blind to the primary outcome of the study, namely incident

depression. Further, the program content of the alternative treatment was not revealed. In sum, participants are blind to study hypotheses and content of other treatment group through study duration.

Investigators and outcome assessors are blind to allocation.

## **9. Safety Monitoring Plan**

Safety monitoring will be conducted throughout the study; therefore, safety concerns will be identified by continuous review of the data by the PI, internal quality assurance checks, and DSMB.

Participants will be given a 24-hour telephone number for calling the physician to feelings of depression or suicide thoughts. In the event that significant medical or psychiatric problems are encountered, the study blind will be broken so that appropriate medical treatment will be provided.

The PI designated appropriately qualified personnel to periodically perform quality assurance checks during and after the study. Such monitoring will provide the opportunity to evaluate the progress of the study and to obtain information about potential problems. The monitor will assure that data are accurate and in agreement with any paper source documentation used, verify that subjects' consent for study participation has been properly obtained and documented, confirm that research subjects entered into the study meet inclusion and exclusion criteria, verify that study procedures are being conducted according to the protocol guidelines, monitor review AEs and SAEs, and assure that all essential documentation required by Good Clinical Practices (GCP) guidelines are appropriately filed. At the end of the study, they will confirm that the site has the appropriate essential documents on file, and advise on storage of study records.

Adverse events are monitored during treatment and at post-intervention to evaluate the presence of adverse events or serious adverse events related to the treatment of insomnia in each group. Specifically, given evidence that sleep restriction and stimulus control, both primary active components of CBTI, have been associated with increased sleepiness, physical fatigue, and deterioration in functioning, the presence of these insomnia related events were monitored in CBT-I and SET. Adverse events were defined as clinically significant worsening of daytime sleepiness or functioning due to sleepiness or fatigue, with clinically significant impairment in daily activities. Specifically, adverse events were systematically defined by evidence of deterioration in sleep during the intervention or at post-intervention, with worsening of severity of insomnia symptoms as compared to baseline as measured using the AIS; change in score > 3 points was considered an adverse event. A serious adverse events was defined as a worsening in sleepiness or functioning that resulted in serious consequence such as an accident or loss of job. Additionally, we monitored whether participants complained about the intervention with reports to an external monitors such as the IRB. During the follow-up, relapse of insomnia disorder was viewed as a failure of the treatment to sustain remission of insomnia, not an adverse event. However, during follow-up, we also monitored severity of depressive symptoms and incident depression as noted above; an adverse event was an incident depression which resulted in hospitalization; a serious adverse event was defined as a depression which resulted in a suicide. Furthermore, we monitored any adverse events including illnesses or death.

An independent Data and Safety Monitoring Board met during the enrollment and follow-up and at trial end to review safety data. The Board was blinded to subjects' actual randomized group assignments but had the opportunity to request at any time that the blind be broken, if concerns arise from the blinded data. Ad hoc meetings were scheduled to be convened if SAEs occurred that were considered at least possibly

related to the study procedures. For the adverse events that occurred the Data and Safety Monitoring Board met and determined whether the event was related to the intervention, if it occurred during the intervention period, or was related or could be attribute to the trial if it occurred during the follow-up,

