A two-year follow-up will be implemented as annual incidence of depression for those with insomnia is estimated to be 13%. We extended follow-up from 24 months to 36 months because rates of depression incidence were found to be lower than expected at 9.6% possibly due to efficacy of treatment of insomnia in both CBT-I and SET groups. For example, the active comparator condition, SET, has benefit on insomnia, and we have found that SET results in a remission of insomnia in about 10% of older adults. Nevertheless the rate of insomnia remission in CBT-I is considerably higher at about 50%.

A total of at least 6, with extension to 8, interview-administered assessments will be completed (entry, post-treatment, and every 6-months for two years with extension to three years) to evaluate depression incidence in the two groups (primary outcome), as well as temporal changes in insomnia and inflammatory markers (secondary outcomes). To determine the emergence of depression with temporal specificity beyond in person assessment every 6 months, we will actively monitor depressive symptoms throughout follow-up by an interactive Automated Telephone Response System (ATRS); subjects will access a tollfree number monthly for administration of the PHQ-9. If their responses suggest the onset of depression with at least moderate depressive symptoms (PHQ-9  $\geq 10$ ), an in person interview will be performed with assessment using the Structured Clinical Interview for diagnostic ascertainment of DSM-5 depression. In addition, if a subject endorses thoughts of death or suicide, subjects will be interviewed on the phone with subsequent in person administration of the SCID to ascertain depression. We have used similar ATRS procedures in the Shingles Prevention Study to identify shingles cases in over 38,000 older adults over a two year follow-up with >95% completion.

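### The two adverse event definitions in the Safety Monitoring Plan do not match, and the AIS rule alone can under-count non-serious sleepiness, fatigue and impaired functioning, probably more in CBT-I

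*Supplement*

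**What the plan says.** Section 9 of the final protocol (Safety Monitoring Plan) takes up the harms of insomnia treatment in three steps.

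- It names the harm. Sleep restriction and stimulus control "have been associated with increased sleepiness, physical fatigue, and deterioration in functioning", and these events were monitored in both arms.
- It gives a definition to match: "Adverse events were defined as clinically significant worsening of daytime sleepiness or functioning due to sleepiness or fatigue", with clinically significant impairment in daily activities. No scale, threshold or set of questions is named.
- The next sentence turns to measurement: "adverse events were systematically defined by evidence of deterioration in sleep during the intervention or at post-intervention". The criterion is "worsening of severity of insomnia symptoms as compared to baseline as measured using the AIS", and "change in score > 3 points was considered an adverse event".

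The same section defines a serious adverse event by sleepiness or functioning with a serious consequence, such as an accident or loss of job, without the AIS. It also says that any adverse events, including illness and death, were monitored.

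Section 6 (CBT-I) warns against restricting the sleep window too far because "this level of restriction can lead to daytime drowsiness and related adverse events which were monitored during treatment", and points forward for the method, which leads to section 9.

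**The concern.** The second definition is worded as the working form of the first, but it measures something else. The stated harm is how the participant feels and functions by day. The AIS, as the protocol describes it in section 5 (Insomnia assessment) and in section 9, scores the severity of insomnia. That is what both treatments aim to lower, and CBT-I is expected to lower it more.

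If the AIS rule is the one used to count events, a CBT-I participant who sleeps better at night but is clinically worse by day may fall short of it. What is at stake is any statement that sleep restriction and stimulus control were well tolerated, or that the arms had similar rates of non-serious events.

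**Working it through.** The plan states no expected adverse event rate and no expected AIS change, so there is no figure to reproduce. The check is a comparison of texts, followed by arithmetic on the threshold.

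**1. The two definitions side by side (section 9)**

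| | First definition | Second definition |
|---|---|---|
| What is measured | Daytime sleepiness or functioning | Deterioration in sleep |
| Instrument | None named | AIS, insomnia severity |
| Threshold | Clinically significant, with impaired daily activities | Rise of more than 3 from baseline |
| Timing | During treatment and at post-intervention | During the intervention or at post-intervention |

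The AIS rule is the only one for non-serious treatment-related events that has an instrument and a threshold. Section 5 (Biobehavioral and medical factors) lists the SF-36 for daily functioning but does not tie it to adverse events.

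**2. Why an under-count would have a direction**

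- Section 4 (Design Overview) expects insomnia remission in about 50% with CBT-I and about 10% with SET.
- Section 6 says sleep restriction induces mild sleep loss while helping sleep onset and continuity. On the protocol's own account, sleepiness and insomnia severity can move in opposite directions.
- Sleep restriction and stimulus control are listed as CBT-I components and are not among the SET topics.

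**3. Distance to the threshold**

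Assume whole-number scoring, so that more than 3 means at least 4 above baseline. If the score has already changed by m (negative for improvement), the further rise needed is 4 − m.

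- m = 0: 4 points
- m = −2: 6 points
- m = −4: 8 points
- m = −6: 10 points

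**4. Illustration with assumed values**

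The documents give no AIS means or SDs. Assume that change is normal with mean m and flagged above 3.5: P = 1 − Φ((3.5 − m)/SD). Assumed ranges: SET mean −1 to −2, CBT-I mean −2.4 to −5, SD 3 to 5. The last column adds the same 3 AIS points of harm to both arms.

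Worked case, SD 4, means −1 (SET) and −4 (CBT-I):
- No added harm: 4.5/4 = 1.125 gives 13.0% in SET; 7.5/4 = 1.875 gives 3.0% in CBT-I.
- With 3 points added: 1.5/4 = 0.375 gives 35.4%; 4.5/4 = 1.125 gives 13.0%.

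| SD | Mean SET / CBT-I | Flagged, no added harm, SET / CBT-I | Flagged, +3 points, SET / CBT-I |
|---|---|---|---|
| 3 | −2 / −5 | 3.3% / 0.2% | 20.2% / 3.3% |
| 4 | −1 / −2.4 | 13.0% / 7.0% | 35.4% / 23.4% |
| 4 | −1 / −4 | 13.0% / 3.0% | 35.4% / 13.0% |
| 4 | −2 / −5 | 8.5% / 1.7% | 26.6% / 8.5% |
| 5 | −1 / −2.4 | 18.4% / 11.9% | 38.2% / 28.1% |

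Over the nine combinations run (three pairs of means at SD 3, 4 and 5), the same added harm raises the flagged share by 16.9 to 24.2 percentage points in SET and by 3.1 to 16.4 in CBT-I. The total flagged with that harm is 1.4 to 6.1 times as high in SET. The direction is the same throughout, and CBT-I is never at zero.

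**5. What this does and does not show**

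The no-harm column shows only that a rise above baseline is rarer where the mean falls more; it contains no sleepiness. The last column assumes that the AIS registers the harm, by an invented 3 points. One mean per arm also ignores worsening early in treatment, which the rule covers. The figures show direction under stated assumptions. They do not estimate missed events.

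The AIS items decide which case applies. If none concerns daytime state, the rule does not register non-serious sleepiness as such in either arm, and the loss falls mostly on the arm given sleep restriction. If some do, the harm registers but is offset by improvement elsewhere in the score.

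**The case against.** The strongest reply is that nothing in section 9 says sleepiness went uncounted. The section says these events were monitored in both arms and defines adverse events by them. The AIS sentence can be read as adding a threshold for one component, deterioration in sleep, and worsening insomnia is a legitimate adverse event in its own right. Other routes also exist: the serious event definition, monitoring of any adverse events, complaints to external monitors, and the Data and Safety Monitoring Board's judgement of relatedness. The AIS items are not given, so overlap with daytime symptoms cannot be excluded. The final statistical plan specifies no between-arm safety test, so the consequence lies in how events are described.

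Most of this stands as a limit on the point. A reader might infer that the rule hides the harm, that affected CBT-I participants are not counted, or that safety favours CBT-I by construction. The documents support none of these, for the reasons just given.

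It does not remove the mismatch. The AIS sentence is worded as the specific, systematic form of the definition before it. The serious event route needs a consequence such as an accident. No systematic question about sleepiness is stated. The Board's relatedness review concerned events that had occurred, so it does not make up for events never recorded.

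**Conclusion.** The point holds as an internal inconsistency with a probable direction. Section 9 has two definitions of a non-serious adverse event that measure different things. The AIS rule, if used alone, can under-count non-serious sleepiness, fatigue and impaired functioning, probably more in CBT-I. This rests on the protocol's own expectations: greater insomnia remission with CBT-I, and mild sleep loss from sleep restriction.

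The size cannot be derived from the documents, since every AIS mean and SD above is assumed. The masking is partial if the AIS covers daytime symptoms. Serious events do not depend on the AIS, and the primary analysis is unaffected.

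**What to change.** Reconcile the two definitions in section 9 so that either one counts as an adverse event. Tabulate by arm, separately:

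- (a) clinically significant worsening of sleepiness, fatigue or functioning, as first defined;
- (b) an AIS rise of more than 3 points from baseline.

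Base any safety statement about sleep restriction or stimulus control on (a), and state how (a) was ascertained.

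If (a) was recorded systematically in both arms, the cost is protocol wording and one safety table. If it was not, rewording cannot recover the data. The report should then say so and should not infer comparable safety from AIS counts. The downside is a somewhat higher reported event count, mainly in CBT-I.

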### Ethical Conduct of the Study

This study is conducted in accordance with all applicable Federal human research protections requirements and the Belmont Principles of respect for persons, beneficence, and justice. The procedures set out in this study are designed to ensure that all study personnel abide by the principles of the ICH GCP Guideline and the Code of Federal Regulations (CFR). The PI confirms this by signing FDA Form 1572.

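### Depression leading to hospital admission is graded below job loss from sleepiness, so the SAE-based trigger for ad hoc DSMB meetings does not cover severe non-fatal depression

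*Supplement*

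**What the plan says.** Section 9 (Safety Monitoring Plan) of the Final Protocol sets two separate seriousness rules.

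- **Sleep-related events**, monitored during treatment and at post-intervention. An SAE is "a worsening in sleepiness or functioning that resulted in serious consequence such as an accident or loss of job".
- **Depression**, introduced for follow-up only: "an adverse event was an incident depression which resulted in hospitalization; a serious adverse event was defined as a depression which resulted in a suicide".

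It then describes the Board's work in four statements.

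- Scheduled review: "An independent Data and Safety Monitoring Board met during the enrollment and follow-up and at trial end to review safety data". No interval is given.
- Extra meetings: "Ad hoc meetings were scheduled to be convened if SAEs occurred that were considered at least possibly" related to study procedures.
- Unblinding: the Board "had the opportunity to request at any time that the blind be broken, if concerns arise from the blinded data".
- Adverse events in general: "For the adverse events that occurred the Data and Safety Monitoring Board met and determined whether the event was related to the intervention". The sentence goes on to cover events in follow-up.

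The section also says that adverse events of any kind, illness and death included, were monitored. It attaches no seriousness criterion to them.

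Section 10 (Ethical Conduct of the Study) says the procedures are designed so that "all study personnel abide by the principles of the ICH GCP Guideline".

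**The concern.** A seriousness grade does two jobs. It decides which events are escalated, and it decides which events enter a count of SAEs by arm. Here the bar differs by type of event. A sleepiness event becomes serious through a consequence for employment, whereas a depressive episode becomes serious only through death by suicide.

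The primary outcome is incident major depression, so a reader comparing the arms on safety would look among the serious events for the gravest non-fatal forms of that outcome. If these are filed as ordinary adverse events, the SAE comparison says nothing about them. They also do not open the only explicit route to an unscheduled Board meeting.

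**Working it through.** No arithmetic applies. The check sets the stated rules side by side (all from Final Protocol section 9 unless noted).

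| Event | Period for which a rule is stated | Stated grade | Meets the ad hoc trigger? |
|---|---|---|---|
| Worsening sleepiness or functioning, with accident or job loss | Treatment, post-intervention | SAE | Yes, if at least possibly related |
| Incident depression with hospital admission | Follow-up | AE | No |
| Depression ending in suicide | Follow-up | SAE | Yes, if at least possibly related |
| Suicide attempt without admission | None | None | Not on the text |
| Depression arising during the 8 weeks of treatment | None | None | Not on the text |

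1. **Unequal thresholds.** Rows 1 and 2 cannot come from one scale of gravity. The periods differ, but the protocol gives no reason for a higher bar in follow-up.
2. **Non-fatal suicidal behaviour.** It has no grade of its own, and reaches the AE level only if it comes with a depression that leads to admission. Yet the exclusion criteria in section 5 bar anyone with a suicide attempt in the past year, so the protocol treats such an event as grave at entry.
3. **Treatment period.** The depression definitions are stated for follow-up. The Final Statistical Plan counts an incident episode as a primary event only if it occurs after treatment is complete. An episode that begins during the 8 weeks is therefore neither a primary event nor a safety event with a stated grade. Only the general monitoring sentence catches it.
4. **The trigger.** It has two conditions: the event is an SAE, and it is at least possibly related to study procedures. A depression admission fails the first, so this route never reaches the question of relatedness. A suicide meets the first but must still meet the second.
5. **The sentence on adverse events.** It says that the Board met and judged relatedness, but not when. If the Board met for each adverse event as it arose, limiting ad hoc meetings to SAEs has no function. If it took adverse events at its scheduled meetings, a depression admission waited for the next one, at an interval that is not given. The text does not settle which.
6. **The GCP commitment.** The documents do not reproduce the guideline's seriousness criteria, so the finding does not rest on them. The inconsistency shows within section 9 alone. The commitment is a further statement with which the definitions have to be squared.

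**The case against.** The strongest reply is that severe depression was watched closely whatever its label.

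- The sentence just after the ad hoc rule says that the Board took up the adverse events that occurred, follow-up included. A depression admission is one of these by definition.
- The Board met during enrollment and follow-up and could ask for unblinding at any time.
- Section 9 adds continuous review by the principal investigator, quality checks that cover AEs and SAEs, a 24-hour telephone line, and breaking of the blind for significant psychiatric problems.
- Section 4 requires a telephone interview and then an in-person diagnostic interview if thoughts of death or suicide are reported.
- Depression is ascertained by monthly questionnaire and six-monthly interview, so episodes in follow-up are counted by arm in any case.

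All of this stands, and it rules out a stronger reading. A reader might infer that the Board could not examine severe depression before a participant had died; the sentence on adverse events contradicts that. A reader might also take depression to be the chief harm that the protocol foresaw. The harms it names for CBT-I are sleepiness, fatigue and impaired functioning, and depression is the efficacy outcome.

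The safeguards do not remove the narrower point. None of them changes the grade of an admission or gives a grade to a suicide attempt. The sentence on adverse events has no timing, so prompt review is not assured. The primary outcome counts episodes and does not separate those that led to admission.

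**Conclusion.** The point holds as a fault in grading and escalation. The protocol states a rule, and that rule places severe non-fatal depression below lesser consequences of sleepiness. The explicit ad hoc trigger therefore does not cover it, and an SAE count built on these definitions would leave depression admissions out. The documents do not show that any such event escaped the Board.

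The size is qualitative. Neither document gives a number of depression admissions or of suicidal acts, or a rate from which to derive one, so no estimate is offered. The inconsistency stands even if no such event occurred. The primary analysis is untouched, because episodes are confirmed by diagnostic interview whatever their safety grade.

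The conclusion assumes that section 9 was applied as written and that any SAE tabulation follows its definitions. Neither document describes an SAE table, so that consequence is conditional. The point should be corrected because it concerns safety and costs little to mend.

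**What to change.** Reconcile three parts of section 9 with one another: the AE and SAE definitions, the ad hoc trigger, and the sentence on Board review of adverse events. The result should be one seriousness definition that applies to both arms, to the treatment period and to follow-up, and that is consistent with the GCP commitment in section 10. Depression leading to hospital admission and non-fatal suicidal behaviour would then be graded on the same scale as the other serious events, and the ad hoc trigger would follow from that grade. State also when the Board reviews adverse events below the serious grade.

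Then regrade the events already recorded and tabulate them again by arm, with depression admissions and suicidal behaviour shown separately.

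The cost is protocol wording and reclassification of recorded events. The downside is a few more SAE reports.
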